## Abstract

**Background:**

The prevention of near and actual cardiopulmonary arrest in hospitalized children is a patient safety imperative. Prevention is contingent upon the timely identification, referral and treatment of children who are deteriorating clinically. We designed and validated a documentation-based system of care to permit identification and referral as well as facilitate provision of timely treatment. We called it the Bedside Paediatric Early Warning System (BedsidePEWS). Here we describe the rationale for the design, intervention and outcomes of the study entitled Evaluating Processes and Outcomes of Children in Hospital (EPOCH).

**Methods/Design:**

EPOCH is a cluster-randomized trial of the BedsidePEWS. The unit of randomization is the participating hospital. Eligible hospitals have a Pediatric Intensive Care Unit (PICU), are anticipated to have organizational stability throughout the study, are not using a severity of illness score in hospital wards and are willing to be randomized. Patients are >37 weeks gestational age and <18 years and are hospitalized in inpatient ward areas during all or part of their hospital admission.

Randomization is to either BedsidePEWS or control (no severity of illness score) in a 1:1 ratio within two strata (<200, ≥200 hospital beds). All-cause hospital mortality is the selected primary outcome. It is objective, independent of do-not-resuscitate status and can be reliably measured. The secondary outcomes include (1) clinical outcomes: clinical deterioration, severity of illness at and during ICU admission, and potentially preventable cardiac arrest; (2) processes of care outcomes: immediate calls for assistance, hospital and ICU readmission, and perceptions of healthcare professionals; and (3) resource utilization: ICU days and use of ICU therapies.

**Discussion:**

Following funding by the Canadian Institutes of Health Research and local ethical approvals, site enrollment started in 2010 and was closed in February 2014. Patient enrollment is anticipated to be complete in July 2015. The results of EPOCH will strengthen the scientific basis for local, regional, provincial and national decision-making and for the recommendations of national and international bodies. If negative, the costs of hospital-wide implementation can be avoided. If positive, EPOCH will have provided a scientific justification for the major system-level changes required for implementation.

Trial registration: NCT01260831 ClinicalTrials.gov date: 14 December 2010.

**Electronic supplementary material:**

The online version of this article (doi:10.1186/s13063-015-0712-3) contains supplementary material, which is available to authorized users.

## Background

The Evaluation of Processes of care and the Outcomes of Children in Hospital (EPOCH) study is a cluster-randomized trial comparing the effect of the Bedside Paediatric Early Warning System (BedsidePEWS) with standard care. The outcomes are clinical, processes of care and resource utilization. Here we describe the rationale for the trial, the intervention and the outcomes used, conflict of interest management and the potential impact of the study.

### The problem and current treatments

Cardiopulmonary arrest occurs in 0.1-20/1000 children in hospital wards [1-4], with hospital survival of 27-50% [5-7]. Despite optimal resuscitation and post-arrest care, in-hospital cardiac arrest is associated with significant mortality and acquired morbidity in survivors [3,6,8-11], making prevention the best strategy [6,8,12-23].

### Prevention of near and actual cardiopulmonary arrest

Prevention of near and actual cardiopulmonary arrest in hospitalized children is a patient safety imperative. Prevention is contingent upon the timely identification, referral and treatment of children whose conditions are clinically deteriorating [24,25]. Preventative strategies have focused on the latter portion of this sequence, primarily through improved access to ICU expertise through deployment of Medical Emergency Teams-Rapid Response Teams (MET-RRT). However, studies addressing methods to identify those in need have been few and of limited quality [26].

### Emergency response teams

To date, MET-RRT have not fulfilled their promise. In adult inpatients, following several positive [27-29] and negative [30-33] single-center studies, a 23-hospital, cluster-randomized clinical trial compared implementation of un-validated calling criteria plus MET-RRT with standard care (no MET-RRT, no explicit calling criteria). The primary outcome was a composite of unexpected death, unplanned ICU admission and cardiac arrest. This negative trial [34] provides several important lessons: (1) calling criteria were met in <50% of patients with urgent ICU admission, suggesting that the criteria did not identify patients at risk. (2) The number of patients without unexpected death, unplanned ICU admission or cardiac arrest, who met one or more of these calling criteria is unknown (similar to pediatric studies) [35-39]. (3) Approximately 90% of the patients who met criteria were referred to ICU teams in both MET and control hospitals, suggesting that the calling criteria added little to the standard model.

In children, only before-and-after studies have been published [35-39], of which one is multi-center [40]. The two studies showing reduced all-cause hospital mortality were performed over 6 [36] and 7½ years [38], influenced the findings of a systematic review of pediatric MET-RRT [41], which include no RCTs, and reinforced the potential for description of time-related improvement [42,43] to be ascribed to MET-RRT. Furthermore, the additional benefit from MET-RRT without appropriate ‘afferent limb’ identification mechanisms may be questionable in hospitals where the efferent limb response-ICU expertise is readily available [25].

### Mechanisms to identify children at risk for near and actual cardiopulmonary arrest

There are eight published pediatric mechanisms to identify children at risk for cardiac arrest [1,35,37,44-47]. The development of most has been methodologically limited [48]. There are four published calling criteria [35,37,46,47]. The Cincinnati criteria include subjective elements and have been modified [35,49]. The Baltimore criteria are subjective and/or triggered by acute medical diagnoses [37]. The Bristol tool is subjective and uses thresholds for the airway (nebulized epinephrine, ‘tiring’) and disability [46]. The Melbourne criteria identified 10/24 (42%) patients who had cardiac arrests in their hospital [38] and similar proportions in other hospitals [40,50].

There are four published pediatric scores [1,44,45,48]. The Brighton score uses behavior, circulatory (color, relative tachycardia) and respiratory (relative tachypnea) domains and ‘persistent vomiting following surgery’ with a range of 0 –11 [44]. Evaluation of this score in a cohort of 2979 children in Cincinnati Children’s Hospital found a sensitivity of 78% and specificity of 82% [49]. In the development cohort, the Cardiff and Vale score had a sensitivity of 69% and specificity of 90%. Inspection of the score reveals that children in the first months of life may be expected to routinely score at or above the threshold (2 points for systolic blood pressure <70 mmHg and respiratory rate >50 breaths/min) [45].

### The BedsidePEWS

The BedsidePEWS score differentiated between children who were urgently admitted to PICU and ‘well’ hospitalized children, with at least 1 h notice with a sensitivity of 83% and specificity of 95% [48]. In a multi-center validation study of 2074 patients the score performed well in sub-populations [51]. Among ‘case patients’ the score increased over time leading up to an urgent PICU admission or code-blue event, and was independent of the number of risk factors for cardiac arrest. [51].

The score was reliably calculated with an intraclass correlation coefficient of 0.92 and was associated with statistically significant improvements in clinical and process of care outcomes [52]. The quality of development, validation and evidence of reliability supports the conclusion that the BedsidePEWS score is equivalent or superior to others and provides a rationale for its use as the intervention in EPOCH (Table 1).

**Table 1 Tab1:** **Differences between BedsidePEWS and other severity of illness scores**

(1)	A validated severity of illness score that is better at identifying patients at risk than the retrospective opinion of frontline nurses
(2)	Complete integration of scoring into routine documentation
(3)	Explicit care recommendations derived from the opinions of 280 healthcare professionals
(4)	Nurse-educator developed, provider tested implementation program
(5)	Pilot evaluation showing improved outcomes without additional resources

The objectives of EPOCH are to evaluate the impact of the BedsidePEWS on early identification of children at risk for near and actual cardiopulmonary arrest, hospital mortality, processes of care and ICU resource utilization. We hypothesize that the BedsidePEWS improves early detection of critical illness, reduces mortality, improves processes of care and does not increase healthcare resource utilization.

## Methods

EPOCH is a cluster-randomized trial comparing the BedsidePEWS with standard care (no severity of illness score) in hospitals with a pediatric intensive care unit (ICU). The unit of randomization is the participating hospital. Eligible hospitals provide care for more than a total of 200 eligible inpatient admissions in eligible inpatient wards each year, have specialized pediatric physicians and have at least one PICU. Eligible inpatient wards are defined as areas where care is provided to children who are admitted to the hospital, other than the NICU, PICU, operating rooms and other designated areas where anesthetist-supervised procedures are performed. Emergency departments that care for admitted patients may be regarded as an eligible ‘ward’ (Table 2). Eligible patients are >37 weeks gestational age and <18 years, and they have received care in an eligible inpatient ward. To ensure that major system changes do not introduce bias, we will exclude hospitals that plan to introduce or discontinue an MET-RRT during the study, are already using a severity of illness score in wards or consider randomization unacceptable. Hospitals with a pre-existing MET-RRT are eligible to participate.

**Table 2 Tab2:** **Study definitions**

Eligible inpatient wards	Areas where care is provided to patients who are admitted to the hospital, other than the PICU, NICU, operating rooms and other designated areas where anesthetist-supervised procedures are performed
	Admitted patients cared for in emergency departments will be regarded as in an eligible ‘ward’ if the documentation format is the same in the emergency department as in the inpatient ward. If the emergency department continues to use a separate ‘emergency department’ documentation record for admitted patients then the emergency department will be deemed an ineligible area
PICU	A PICU is defined as a designated staffed area for prolonged mechanical ventilation, invasive monitoring and circulatory support for children, including but not limited to neonates. Other areas designated for patients of increased acuity, such as ‘constant observation’ or ‘high dependency’ or ‘step-down’ units, will be regarded as part of the PICU where the PICU staff physicians are wholly or jointly responsible for the care of children in these areas (can write orders in the chart). Routinely admitted patients will include children beyond the neonatal period who are <12 years of age at admission
MET-RRT	An MET-RRT is defined as an identified team of one or more trained healthcare professionals who report to an on-service PICU physician and perform urgent consultations on hospital inpatients. An MET-RRT ‘call’ is analogous to an ICU consultation in hospitals without an MET-RRT. As the effectors of expertise, the impact of the MET-RRT (or other ICU team) is dependent upon appropriate identification of patients at risk and timely referral
Urgent PICU admission	An admission to the PICU with departure from the event location in <6 h from the time the PICU admission was initiated. Initiation is the time when the PICU admission is confirmed, or confirmed as a ‘definite possibility following surgery’ in cases where post-operative care in the PICU might be required. PICU admissions initiated in the OR are also regarded as urgent ICU admissions, irrespective of the time between initiation and departure from the OR
Time of transfer	Transfer is when a patient is transferred urgently to a pediatric intensive care unit (PICU) in the participating hospital. The time of transfer is the arrival in the PICU. When a patient is admitted urgently from an eligible hospital ward to a PICU via a procedure in the OR, the time of transfer to the ‘PICU’ is regarded as beginning at the time of departure from the inpatient ward to the operating room. Treatments other than cardiopulmonary resuscitation provided in the operating room are not included in the calculation of the clinical deterioration event. Unexpected events occurring in the operating room that require postoperative/post-anesthetic care in the PICU, in patients who were not anticipated to require PICU at the time the patient was transferred from the inpatient ward to the operating room, will not be regarded as clinical deterioration events
Study Day	Study days are calendar days; they begin at 00:00:00 and end at 23:59:59
Study weeks	begin on Monday and end on Sunday. The first week of the study is study week 01

### Intervention: BedsidePEWS

The BedsidePEWS documentation-based system of care replaces existing documentation systems for vital signs in inpatient ward areas in hospitals randomized to the intervention. There are four elements in the system: (1) the BedsidePEWS score; (2) the BedsidePEWS documentation record; (3) score-matched care recommendations, developed using the responses of 280 healthcare professionals (80 community, 200 referral) surveyed to determine ‘reasonable’ care in each of the domains of vital sign assessment, secondary review, continuous monitoring and ICU consultation, and customized for each implementation; (4) the education program, developed by two nurse educators to support implementation and maintain expertise, including the BedsidePEWS Instructor course and frontline education program.

### Randomization

Participating hospitals are randomized in a 1:1 ratio to intervention or control. Computerized randomization is balanced by the use of two strata of hospital size: <200 vs. ≥200 eligible inpatient ward beds. Allocation is concealed until the start of the study measurements and is revealed in the 2nd week after the start of data collection at each site (Additional file 1).

### Primary outcome: all-cause hospital mortality

The primary outcome is all-cause hospital mortality in eligible inpatients who were cared for in an eligible inpatient ward at some point during their hospital stay. This includes anticipated deaths in children with ‘do not resuscitate’ orders. Mortality events in children cared for exclusively in the PICU, NICU or emergency department, or combinations thereof, are excluded.

### Secondary outcomes: clinical

The main secondary outcome is the significant clinical deterioration event (SCDE), a composite outcome comprised of the treatment(s) provided or death prior to transfer from an inpatient ward. An SCDE is defined as the provision of significant pre-specified respiratory or circulatory therapies or cardiopulmonary resuscitation in the 12 h before transfer from the inpatient ward or during the hour after transfer, or death without a DNR order in an inpatient ward (Table 2).

EPOCH includes eight additional clinical outcomes (Table 3): (1) the nature of SCDE rated on the seven-point Children’s Resuscitation Intensity Scale (Table 4), which measures the timing of interventions in children for whom active resuscitation is anticipated; (2) potentially preventable cardiac arrest in patients experiencing a cardiac arrest while in an eligible inpatient ward. This excludes patients with a preceding DNR order. Potentially preventable is defined as the degree to which ‘events may have been avoided given the application of reasonable current (2011-13) standards of practice by an average practitioner and system anticipated to manage the condition in question’ [53-57]. Events with a consensus rating from two expert reviewers of ≥4/6 are defined as potentially preventable cardiac arrests (Table 5) [55,56]. (3) Unplanned hospital re-admission; (4) urgent PICU re-admission, both within 48 h of discharge. Finally, in all patients admitted urgently to the PICU from a hospital inpatient ward measurement was made of: (5) the predicted risk of mortality (PIM2 score) [58,59], (6) PICU mortality, (7) organ dysfunction (PELOD score) [60] and (8) ventilator-free days to 28 days. Urgent PICU admission is defined as departure from the inpatient ward within 6 h of the decision to admit to the ICU (Table 2). This definition reflects the need to pragmatically distinguish between urgent and elective admission and the recognition that most urgent admission occurs within 1-2 h of the decision to transfer to an ICU.

**Table 3 Tab3:** **EPOCH secondary outcomes**

**Clinical**	
(1) Significant clinical deterioration event	See Table 4
(2) The nature of clinical deterioration events	Clinical deterioration events will be described by using the Children’s Resuscitation Intensity Scale (Table 4). Urgent PICU admissions that are initiated when the patient is in the operating room will not be regarded as clinical deterioration events
(3) Potentially preventable cardiac arrest	Assessment of the potential preventability of cardiac arrest will be determined for all patients who had a cardiac arrest event while in an eligible inpatient ward, without a preceding DNR order (Table 5)
	Thus, potential preventability ratings of 4: ‘more than likely (more than 50/50, but “close call”);’ 5: ‘strong evidence of preventability;’ 6: ‘virtually certain evidence of preventability’ will be deemed potentially preventable cardiac arrest events
	Preventability will be rated by blinded reviewers reviewing anonymized and delinked clinical data presented in a standardized format. If consensus between the two initial reviewers still cannot be reached then the opinion of the third reviewer will be used as the consensus rating
(4) Unplanned re-admission to the hospital within 48 h of hospital discharge	This outcome will be operationalized as re-admission before midnight of the second day full day after discharge. Thus, re-admission will occur before the 3rd midnight following hospital discharge
(5) Unplanned PICU readmission within 2 days of PICU discharge	This outcome will be operationalized as re-admission before midnight of the second full day after discharge. Thus, re-admission will occur before the 3rd midnight following PICU discharge
(6) PIM score predicted the risk of mortality	
(7) PICU mortality.	
(8) The PELOD score for PICU stay and the first 24 h in PICU	This score will be determined for both the entire PICU stay and the first 24 h in the PICU
(9) Ventilator-free days	Days alive and without invasive mechanical ventilation in the 28 days beginning at PICU admission will be recorded for the first PICU admission during each of the baseline and the post-randomization periods
Process of care	
(1) ‘Stat’ calls to physicians	Requests for immediate specific physician attendance to provide patient care to a patient admitted to an inpatient ward
(2) Code Blue calls	Immediate medical assistance of the resuscitation team and equipment

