#### Secondary analyses

An identical logit model will be used for ICU mortality after urgent ICU admission where the PICU admission was initiated in a hospital ward, ICU mortality after urgent ICU admission initiated in the OR, unplanned hospital re-admission within 2 days of hospital discharge and mortality following DNR orders.

Significant clinical deterioration events, Code Blue events, stat calls and urgent PICU consultations per 1000 patient-days will be evaluated using Poisson regression using hospital-level aggregated count data. The independent variables will include a dummy indicator for treatment arm, the baseline event rate and hospital size stratification variable. A linear regression model, in which the within-hospital mean is the dependent variable, will be used to evaluate the nature of SCDE, inpatient ward patient-days, and for patients admitted urgently to the PICU, PIM2 score, PELOD score, ventilator-free days, ICU patient-days and ICU therapy-days. The independent variables will include a dummy indicator for treatment arm, the baseline means and hospital size stratification variable. The analysis will be weighted by the size of the hospital.

An identical linear regression model will be used to evaluate the frequency of vital sign documentation from the randomly selected patient records. Since the number of records abstracted will be the same in each hospital, weighting will not be necessary. Documentation will be evaluated as follows: the number of heart rate, respiratory rate, systolic blood pressure, trans-cutaneous oxygen saturation, capillary refill, oxygen therapy and respiratory effort measurements, and the number of times that all seven items were documented will be compared for patients in hospitals with and without BedsidePEWS. All analyses will adjust for baseline event rates and hospital strata. Linear regression will be used to compare the numbers of (1) vital signs documented, (2) documented physician visits, (3) the nurse: patient ratio, the use of (4) continuous ECG monitoring and (5) continuous pulse oximeter monitoring with the BedsidePEWS scores calculated from the abstracted clinical data.

Analysis of the documentation and interaction survey and the post-study decision-maker survey data will compare groups using linear regression weighted by the size of the hospital.

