As well, all-cause mortality is an established quality metric in Canadian and British adult hospitals and is publicly reported as the standardized mortality ratio in Ontario Hospitals [68,69,78-80]. Finally, while death ‘with DNR’ vs. ‘unexpected’ deaths (no DNR) has been used to distinguish ‘preventable’ from ‘unpreventable’ deaths following acute events in adult patients [34,81], in hospitalized children there are significant limitations to this distinction: (1) DNR orders reflect current expectations of outcome and not the ‘preventability’ of the preceding clinical events; (2) the majority of deaths in hospitalized children, especially in the ICU, occur some days after a clinical deterioration event [3,7,10,18,21,82], but within a relatively short time (hours) between DNR order and death [83-85]. Before confirming that a death in a patient with a DNR order was truly unpreventable, the clinical context and timeline of clinical deterioration prior to the DNR order must be known. It must also be recognized that medically ‘futile’ resuscitation may be performed on hospitalized children [86] for whom no DNR order is in place.

EPOCH outcomes are assessed for 1 year after hospital-wide implementation of intervention or continuation of standard care. This duration was chosen to reduce the effects of seasonal variation, but also to reduce the burden of a multi-year intervention period on each hospital, thus increasing feasibility, and to support timely completion of the study to support the decision-making needs of administrators. Continued eligibility will be confirmed by intermittent reporting of the MET-RRT and Early Warning Score use during the course of the study.

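### Ventilator-free days penalise death only through the days lost after it, so a child who dies late off the ventilator can outscore a survivor ventilated for longer

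*Protocol article*

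**What the plan says.** Table 3, clinical item 9, gives the operational rule: "Days alive and without invasive mechanical ventilation in the 28 days beginning at PICU admission will be recorded", for the first PICU admission in each study period. Under Secondary outcomes: clinical, the measure appears as "ventilator-free days to 28 days". Its population is set there by the statement that "in all patients admitted urgently to the PICU from a hospital inpatient ward measurement was made of" this and three other outcomes, so children who later die are included. PICU mortality is one of those other outcomes and is reported separately.

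Under Secondary analyses the method is "A linear regression model, in which the within-hospital mean is the dependent variable", applied to a list that includes "PIM2 score, PELOD score, ventilator-free days, ICU patient-days and ICU therapy-days". The model has terms for treatment arm, baseline mean and hospital-size stratum, and is weighted by hospital size. Nowhere does the article give death a score of 0 or a worst rank on this outcome.

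**The concern.** The count combines two things: how long a child lived within the window and how long the child was off the ventilator. A day off the ventilator before death is worth as much as a day off the ventilator in a child who recovers. A late death with little ventilation can therefore rank above a survival with more ventilation.

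In a trial whose primary outcome is death, a reader will take more ventilator-free days as a better result. With this rule that reading is not safe. A hospital mean can be higher because survivors came off ventilation sooner, or because children who died had spent more days off the ventilator first. The Discussion gives reason to expect deaths inside the window, since "the majority of deaths in hospitalized children, especially in the ICU, occur some days after a clinical deterioration event".

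**Working it through.** The article states no expected value, power or sample size for this outcome, so there is no figure to reproduce. The check applies the definition directly.

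**Scores for individual children.** Let v be days of invasive ventilation and D the day of death, with the day of death counted as a day alive.

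- Present rule, survivor: 28 − v. Present rule, death on day D ≤ 28: D − v.
- Alternative rule, survivor: 28 − v. Alternative rule, death by day 28: 0.

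| Child | Present rule | Death = 0 |
|---|---|---|
| Never ventilated, dies day 20 | 20 − 0 = 20 | 0 |
| Ventilated 2 days, dies day 20 | 20 − 2 = 18 | 0 |
| Ventilated 10 days, then off, dies day 12 | 12 − 10 = 2 | 0 |
| Ventilated 10 days, stopped and dies day 10 | 10 − 10 = 0 | 0 |
| Survivor, ventilated 10 days | 28 − 10 = 18 | 18 |
| Survivor, ventilated 14 days | 28 − 14 = 14 | 14 |
| Survivor, ventilated 20 days | 28 − 20 = 8 | 8 |

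If the day of death is not counted, each score for a child who dies with at least one credited day falls by 1. The first row becomes 19, still above 18.

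**When the order reverses.** A child who dies outscores a survivor ventilated V days when D − v > 28 − V, that is, when V − v > 28 − D. The survivor's extra ventilation days must exceed the days lost to death. For a never-ventilated child (v = 0), this happens for deaths from day 22 on against V = 7, from day 15 on against V = 14, and from day 9 on against V = 20.

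**Shift in a hospital mean.** Relative to scoring death as 0, the mean rises by m × c, where m is the proportion dying within 28 days and c is the mean days credited to them. The documents give neither, so both are assumptions.

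- m = 5%, c = 3: 0.05 × 3 = 0.15 days.
- m = 10%, c = 6: 0.10 × 6 = 0.6 days.
- Wider range, m = 3-15% and c = 0.5-10: from 0.03 × 0.5 = 0.015 to 0.15 × 10 = 1.5 days.

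The only loose ceiling on m comes from the Discussion, which expects about 500 deaths and 1900 urgent ICU admissions. If every death followed such an admission, m would be 500/1900, about 26%.

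**Arm comparison.** The contribution is the difference between arms in m × c after adjustment for baseline means. If m × c is similar in both arms, it largely cancels. No input for this difference is available.

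**The case against.** The strongest reply is that death is already penalised. No day after death counts, so a child who dies on day 8 loses at least 20 of the 28 days, and dying never raises a child's score above what the same child would have had by surviving off the ventilator. The count is coherent as a measure of days alive and off ventilation. Mortality is also visible elsewhere, as the primary outcome and as PICU mortality in the same children. All of this stands, and it keeps the point minor. It does not restore the ordering between different children.

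A reader might infer something stronger: that the outcome rewards death, or that hospitals which stop ventilation before death would gain enough to bias the comparison. The documents do not support that. The Discussion describes death as coming "within a relatively short time (hours) between DNR order and death". If ventilation is stopped at about that point, the child gains roughly no credited days, as the same-day row of the table shows. The larger credit goes to children already off the ventilator for days before dying, and how often that happens is not stated. The model also adjusts for each hospital's mean over the 26-week baseline, which absorbs part of any stable difference in practice. Only a change that differs by arm would distort the comparison, and nothing in the article points to one.

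It could also be said that a fuller analysis plan may settle the scoring. But Table 3 states the count explicitly, so a plan that scored death as 0 would depart from the published definition.

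**Conclusion.** The concern holds in a limited form. By the wording of Table 3, some children who die score above some who survive, and those scores pass unchanged into the analysed hospital means. The outcome therefore cannot be read simply as higher is better.

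The ordering problem is exact and needs no assumption beyond how the day of death is counted. The size in the mean, 0.15-0.6 days on the central assumptions and 0.015-1.5 days on the wider ones, rests on mortality and credited days that the documents do not give. It is a shift that can occur in both arms and is not a demonstrated bias; the effect on the treatment comparison cannot be derived. One unpowered secondary outcome is affected, and the primary analysis is not. Severity is low: a cheap improvement, not a required correction.

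**What to change.** In Table 3, item 9, state that ventilator-free days equal 0 for any child known to have died in hospital within 28 days of PICU admission, whatever the ventilation status before death, and equal 28 minus days of invasive ventilation for survivors. Survivors' scores do not change, and no child who dies can then outscore a survivor. Hospital deaths and ventilator days are already collected.

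If the present count is preferred, label it *days alive and off invasive ventilation* and report it as supplementary, beside mortality.

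The cost of the first option is one sentence and some loss of information. Deaths on day 1 and day 27 tie with each other and with survivors ventilated for all 28 days, the mean is lower and more skewed, and the outcome overlaps more with mortality.
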